## 2.10 Statistical analysis

For the primary outcome, the tooth will be the unit of analysis and the Kaplan-Meier test will be performed to estimate the survival rates of the included teeth. In addition, we performed an intention-to-treat (ITT) analysis, considering follow-up successes and failures. For comparison between the two groups, Student's t test or Mann-Whitney test will be performed, depending on the normality of the data. In addition, Poisson regression analyzes will be carried out, in order to allow the evaluation of the influence of some variables on the results. For all analyses, the significance value will be adjusted to 5%.

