#### 2.5.1 Inclusion criteria

Children aged 3 to 6 years, with at least one anterior deciduous tooth with irreversible pulpitis or pulp necrosis due to caries or trauma, with at least 2/3 of root remaining, and children who have not undergone antibiotic therapy within three months previous.

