#### 2.9 Clinical and radiographic evaluations of selected teeth

Clinical evaluations will be considered as the primary outcome and will be performed in a dental chair under the light of a reflector, using a clinical oral mirror and palpation of the affected tooth area. At the initial examination and at the 1, 3 and 6 month follow-up examinations, the following clinical data will be recorded: history of spontaneous pain indicative of apical periodontitis, presence of fistula or abscess, presence of gingival edema, and pathological mobility. As a secondary outcome, signs of radiolucency in the periapical region and pathological root resorption will be evaluated radiographically.

The clinical data collected in the initial examination and in the control of 1, 3 and 6 months after the treatment and the comparison of the initial radiograph for diagnosis with the radiographs taken in the control exams will be the basis for evaluating the success or failure of the endodontic therapy. The radiographs will be analyzed by two experienced and trained professionals, with the aid of a negatoscope. These professionals will not have any information regarding the treatment group to which each tooth belonged and, in case of doubts during the evaluation, a consensus between the examiners will be established.

The following criteria will be used to determine the success or failure of the proposed treatment, according to the work by Chan et al 15:

|                                  |                                                                                                                                                                                                                                                                                                                                                                                               |
|----------------------------------|-----------------------------------------------------------------------------------------------------------------------------------------------------------------------------------------------------------------------------------------------------------------------------------------------------------------------------------------------------------------------------------------------|

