| 1. Complete repair (=success)    | Clinically : absence of signs and symptoms.
radiographically : absence of pathological root resorption, normal width of the periodontal ligament space, absence of lesion development in the periapical region in cases of absence of lesion observed in the initial radiograph for diagnosis and total regression of the lesion when present at the beginning of treatment. |
| 2. Incomplete repair (= success) | Clinically : absence of signs and symptoms.
radiographically : absence of pathological root resorption and reduction in size of the lesion in the periapical region.                                                                                                                                                                                                         |
| 3. Failure to repair (= failure) | Clinically : signs and symptoms indicative of apical periodontitis in the acute phase.
radiographically : presence of pathological root resorption, lesion in the furcation/periapical region of unchanged size during the follow-up period, enlargement or development of a new radiographic lesion.                                                                        |

All radiographs will be standardized using adult periapical film (Kodak, Rochester, NY, USA) in the occlusal position (modified occlusal radiograph).

The same development time, intermediate wash, fixation and final wash at all evaluation times will be used to standardize radiography processing.

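### Kaplan-Meier survival is a poor match for a primary outcome defined as repair, which can change between visits; the event is undefined, and 6-month success should be the primary quantity

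*Protocol*

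**What the plan says.** Section 2.10 assigns the primary outcome to a survival method: "For the primary outcome, the tooth will be the unit of analysis and the Kaplan-Meier test will be performed to estimate the survival rates". It adds, in the past tense, "we performed an intention-to-treat (ITT) analysis, considering follow-up successes and failures", without naming a visit. The comparison between groups is given to Student's t test or the Mann-Whitney test. No section says what counts as the Kaplan-Meier event, or whether a tooth that falls short at one visit can later count as a success.

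Section 2.9 says "Clinical evaluations will be considered as the primary outcome" and makes radiographic signs secondary. On timing it says "At the initial examination and at the 1, 3 and 6 month follow-up examinations, the following clinical data will be recorded". Besides a history of spontaneous pain, the recorded items are "presence of fistula or abscess, presence of gingival edema, and pathological mobility". The same items are therefore recorded before treatment and at each later visit.

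The table in 2.9 grades repair. Clinically, both success categories require that no sign or symptom remains, while failure requires indications of apical periodontitis in its acute phase. Radiographically, complete repair includes "total regression of the lesion when present at the beginning of treatment". A lesion that has shrunk is incomplete repair and counts as success. A lesion whose size has not changed over follow-up is a failure.

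Section 2.5.1 admits children with "at least one anterior deciduous tooth with irreversible pulpitis or pulp necrosis due to caries or trauma". Section 2.4 assumes a 12-month success rate of 86.4% for CTZ and a non-inferiority limit of 15%.

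**The concern.** A Kaplan-Meier curve describes the time to a first event in units that are free of that event at time zero, and the event cannot be undone. The outcome in 2.9 works differently. Teeth are treated because they are diseased, some may carry a recorded sign on day 0, and the question is whether that sign goes away. A tooth can be short of success at 1 month and fully repaired at 6 months.

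A first-event curve would mix how fast early signs resolve with whether treatment finally works. Two pastes with the same 6-month success could look different, or a real difference could be hidden. Section 2.4, by contrast, plans on a success proportion with a 15% limit, and a first-event curve does not estimate that proportion when status can reverse. If the event is chosen only after the data are seen, that choice could affect the non-inferiority conclusion.

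**Working it through.** **Setting the sections side by side**

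1. Method (2.10): survival of teeth, with no event stated.
2. Outcome (2.9): absence of signs for clinical success, acute-phase signs for clinical failure. Consider a tooth with a non-acute fistula or residual mobility at 1 month. It is not a success, because a sign is present. It is not clearly a failure, because the sign is not acute. The table leaves it unclassified.
3. If the event is the first visit that does not meet success, that tooth has its event at month 1 and keeps it, even if 2.9 would grade it as complete repair at month 6.
4. If the event is loss of the tooth, the curve does not analyse the clinical outcome that 2.9 calls primary.
5. Planning quantity (2.4): a success rate with a 15% limit. Neither reading of the curve gives that quantity when status can reverse.

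**Size under the first-event reading**

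The protocol gives no figure for this effect, so there is none to reproduce. The inputs are:

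- S, success at 6 months: 0.864 in both arms. This borrows the 12-month planning rate for CTZ in 2.4, and using it at 6 months and for both pastes is an assumption.
- b, the share of eventually successful teeth with a clinical sign at baseline: assumed 0.25, 0.50 or 0.75.
- q, the share of those teeth still showing the sign at 1 or 3 months but healed by 6 months: assumed 0.10 in one arm and 0.30 in the other.

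With no losses, the Kaplan-Meier estimate at 6 months is the share of teeth with no event at any visit. Teeth not successful at 6 months count against both measures. Among the rest, only late resolution of a baseline sign is taken to produce an event. Hence:

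Kaplan-Meier at 6 months = S × (1 − b × q)

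Artificial arm difference = S × b × (0.30 − 0.10)

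| b | Estimate, q = 0.10 | Estimate, q = 0.30 | Difference |
|---|---|---|---|
| 0.25 | 0.864 × 0.975 = 84.2% | 0.864 × 0.925 = 79.9% | 4.3 points |
| 0.50 | 0.864 × 0.950 = 82.1% | 0.864 × 0.850 = 73.4% | 8.6 points |
| 0.75 | 0.864 × 0.925 = 79.9% | 0.864 × 0.775 = 67.0% | 13.0 points |

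Differences are taken before rounding. In every row the 6-month success is 86.4% in both arms, so the true difference is zero.

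If both pastes heal at the same speed, no artificial difference arises but the level is too low. With b = 0.50 and q = 0.20 in both arms, the estimate is 0.864 × 0.90 = 77.8%, which is 8.6 points below 86.4%.

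**The case against.** The strongest reply is that the harm rests on a rule the protocol does not contain, and that defining the event is commonly left to a statistical analysis plan, which is not at hand. Much of this is fair, and several stronger readings that a reader might infer are not supported.

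- *Early signs are permanent failures under the plan.* Section 2.10 defines no event, so this is one possible reading only. Section 2.9 also says that the data from all visits together form the basis for judging success or failure, which fits a single overall judgement.
- *All teeth enter with the signs that define failure.* Section 2.5.1 requires pulpitis or necrosis and none of the recorded signs. Baseline signs are plausible: the Introduction lists mobility and furcation radiolucency among the indications for the technique, and the Summary has fistula and mobility assessed on the day of treatment. They are not a condition of entry.
- *A lesion still resolving counts as a failure.* It does not. A shrinking lesion is a success, an unchanged one is judged over the follow-up period, and radiographic signs are secondary. The problem lies mainly with persisting clinical signs.
- *The 15% limit will be tested on the Kaplan-Meier difference.* No section says so. Section 2.10 gives the group comparison to other tests, and the intention-to-treat analysis could use 6-month status.

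What remains is a mismatch within the protocol itself. It fixes both the method for the primary outcome and the criteria for that outcome, and the two do not fit. The intention-to-treat sentence is an addition and names no visit, so it does not repair this.

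**Conclusion.** The point holds in a limited form. The stated primary analysis is a poor match for an outcome that is repair and can change between visits, the Kaplan-Meier event is not fixed, and the clinical criteria leave a persisting non-acute sign unclassified. This should be settled before results are known.

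The size is illustrative. The range of about 4 to 13 points, against a 15-point limit, applies only if the first visit short of success is the event. It also depends on the assumed baseline-sign shares, on the assumed 10% and 30% late resolution, and on using the 12-month rate as 6-month success in both arms. A reader might take 13 points as the expected bias. It is the top of the assumed range, and equal healing speed gives no artificial arm difference. Nor do the documents support saying that the trial cannot estimate effectiveness: the data for 6-month success are already to be collected.

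**What to change.** In 2.10, make the primary quantity the proportion of teeth with success at the 6-month examination, compared between arms as a difference with a confidence interval against the 15% limit of 2.4. Keep Kaplan-Meier as a supportive analysis and state its event, including how a baseline sign that persists at 1 or 3 months is handled.

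In 2.9, reconcile the clinical wording for success and failure so that every tooth falls into one category at 6 months. The trial team should decide which category takes a persisting non-acute sign.

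The cost is a change of wording in two sections, because the baseline and 1, 3 and 6 month data are already planned. There are two small downsides. Teeth lost before 6 months will need a missing-data rule in place of censoring, and early persisting signs will be reported descriptively.

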### 2.4 Determination of sample size

To carry out the sample calculation, a 12-month success rate for the CTZ paste of 86.4% was assumed. The non-inferiority limit was considered as 15%, power of 80% and significance level of 5%, which resulted in 38 teeth per group. 20% were added to this number due to possible sample losses and 40% due to the patient having more than one tooth included, resulting in a sample of 60 deciduous anterior teeth per group, totaling 120 deciduous anterior teeth.

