### 2.7 Randomization

The type of treatment will be randomly determined for each tooth, through a draw before the intervention. The draw will follow the order electronically generated by the randomizer.org randomization website for a balanced distribution of all teeth between the groups.

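### Section 2.4 adds 40% to the sample because children may contribute several teeth, but no method in section 2.10 takes account of the child

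*Protocol*

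**What the plan says.** Three sections of the protocol bear on this.

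- Section 2.4 starts from 38 teeth per group and enlarges this: "20% were added to this number due to possible sample losses and 40% due to the patient having more than one tooth included". The result is 60 teeth per group, 120 in all. Neither an ICC nor a mean number of teeth per child is given. Section 2.5.1 asks for at least one eligible tooth and sets no maximum.
- Section 2.7 allocates by tooth: "The type of treatment will be randomly determined for each tooth". Nothing keeps a child's teeth together or splits them evenly between the pastes.
- Section 2.10 says of the primary outcome that "the tooth will be the unit of analysis and the Kaplan-Meier test will be performed to estimate the survival rates of the included teeth". The groups are compared by Student's t test or the Mann-Whitney test, depending on normality. In addition, "Poisson regression analyzes will be carried out, in order to allow the evaluation of the influence of some variables on the results". The variance estimator for the Poisson model is not named.

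**The concern.** The sample size section accepts that teeth from one child carry less information than the same number of teeth from different children. The analysis section then treats all teeth as independent. Kaplan-Meier with its usual variance and a two-sample t or Mann-Whitney test have no term for the child. What is at stake is the width of the intervals around each paste's success or survival rate, and whether the error rate of a non-inferiority comparison depends on how the teeth in one mouth happen to fall between the arms.

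**Working it through.** **Inputs.** From section 2.4: 86.4% success (CTZ), 38 teeth per group before and 60 after inflation, additions of 20% and 40%. From section 2.7: a draw per tooth. Assumed, because the protocol does not give them: m = 2 to 4 teeth per child and ICC = 0.2 to 0.6.

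**1. The plan's own figure.** The step from 38 to 60 is additive: 38 × (1 + 0.20 + 0.40) = 60.8, stated as 60. Compounding would give 38 × 1.2 × 1.4 = 63.8. The 40% thus acts as a multiplier of about 1.4 for several teeth per child. (The 38 does not follow from the stated inputs with equal rates in both arms: 2 × 0.864 × 0.136 × (1.645 + 0.842)² / 0.15² gives 65 at one-sided 5%. That is a separate matter and is not used here.)

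**2. Rate in one arm.** Under a per-tooth draw, about half of a child's other teeth fall in the same arm, so the design effect is about 1 + (m − 1) × ICC / 2.

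| m | ICC | Design effect | Naive SE / true SE |
|---|---|---|---|
| 2 | 0.2 | 1.1 | 0.95 |
| 2 | 0.4 | 1.2 | 0.91 |
| 3 | 0.2 | 1.2 | 0.91 |
| 4 | 0.4 | 1.6 | 0.79 |
| 4 | 0.6 | 1.9 | 0.73 |

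The last column is 1/√(design effect). Simulation with 120 teeth over these ranges gives 1.11 to 1.89, in agreement.

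**3. Difference between arms.** Pairs of teeth in the same arm raise the variance of the difference, and pairs in opposite arms lower it. With two teeth per child and 60 per arm, the true variance over the naive variance is 1 + ICC × (S − D)/60, where S is the number of children whose teeth share an arm, D the number whose teeth are split, and S + D = 60. At ICC 0.4:

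- all split: 1 − 0.4 = 0.6, so naive SE / true SE = 1/√0.6 = 1.29 (1.27 simulated);
- all sharing: 1 + 0.4 = 1.4, so 1/√1.4 = 0.845 (0.84 simulated). A nominal two-sided 5% test then has error 2 × [1 − Φ(1.96/√1.4)] = 9.8%;
- drawn per tooth: S and D are equal on average, so the ratio is about 1. S has standard deviation of about √(60 × 0.25) = 3.87, so the variance ratio has standard deviation 0.4 × 2 × 3.87/60 = 0.05. Two standard deviations either way give a naive SE between about 0.95 and 1.05 of the truth.

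Simulation of the per-tooth draw over the full assumed range gives variance ratios of 1.00 to 1.03 and 95% interval coverage of 94.0% to 94.5%.

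**4. The 40% against the draw.** A design effect of 1.4 on the comparison is what 1 + (m − 1) × ICC gives when whole children are allocated, for example m = 2 with ICC 0.4, or m = 3 with ICC 0.2. Under the draw in section 2.7 the same values give about 1.0 for the comparison and 1.2 for a single arm.

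**5. Poisson regression.** For a binary outcome with event probability q, the model-based Poisson SE exceeds the binomial SE on the log scale by 1/√(1 − q). Modelling success (q = 0.864) gives 1/√0.136 = 2.71. Modelling failure (q = 0.136) gives 1/√0.864 = 1.08. With 60 teeth per arm, the SE of the log risk ratio is 0.196 against 0.072 for success, and 0.495 against 0.460 for failure. These intervals are too wide, not too narrow.

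**The case against.** The strongest reply is that the comparison the trial exists to make is hardly affected. The draw is per tooth, so same-arm and opposite-arm correlations nearly cancel, as step 3 shows. This stands. A reader might infer that the non-inferiority comparison carries a type I error near 10%. That needs a child's teeth to share an arm, which section 2.7 does not arrange. The conservative figure of 1.27 likewise needs every pair to be split.

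A second reply is that the Kaplan-Meier estimates are descriptive and that the upper design effects come from assumed values beyond what a 1.4 multiplier suggests. This stands in part: values consistent with 1.4 give about 1.2 per arm, not 1.9. But these are the survival estimates that section 2.10 names for the primary outcome.

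A third reply is that a statistical analysis plan not at hand may deal with the child. For the Poisson model this has force. A reader might infer that an ordinary model-based variance is planned, but the protocol is silent, and the regression is an additional analysis, not the named group comparison. For the primary outcome the reply is weaker: section 2.10 itself fixes the tooth as the unit and names the tests, so a later plan that clustered on the child would have to depart from the named comparison. A paired form of those tests would not help, because neither the eligibility criteria nor the draw gives every child one tooth per arm.

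**Conclusion.** The point holds, with limited size. Section 2.4 allows for several teeth per child and section 2.10 has no method that uses the child. Per-arm intervals would be too narrow, with a design effect of about 1.2 at values consistent with the plan's own 40% and 1.1 to 1.9 over the assumed range. The between-arm comparison is close to right on average under the per-tooth draw, and is off in either direction only if the realised allocation is lopsided. All of this rests on assumed teeth per child and ICC.

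Two stronger statements are not supported. The protocol reports no standard errors or intervals, so it cannot be said that stated ones are wrong; the point concerns those that the named methods would produce. Nor do the errors all run one way: per-arm intervals come out too narrow, the comparison about right, and Poisson intervals too wide if a model-based variance were used.

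The 40% is also unexplained: as a design effect on the comparison it does not match a per-tooth draw.

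**What to change.** In section 2.10:

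- record a child identifier for every tooth;
- replace the t test or Mann-Whitney test with a between-arm comparison of success by GEE or with a robust variance clustered on the child, which is suitable however the teeth fall between the arms;
- use a child-clustered variance for the Kaplan-Meier estimates;
- state that the Poisson regression uses a robust variance clustered on the child, which deals with both the correlation and the binary outcome.

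In section 2.4, state the ICC and mean number of teeth per child behind the 40%, and whether it is meant for the comparison or for the per-arm rates, so that it agrees with the draw in section 2.7.

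The cost is a few sentences in section 2.10, one or two in section 2.4, and one variable in the data set. Allocation and the number of teeth need not change for this point.

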## **2. METHODS**

### **2.1 Main goal**

The aim of this study is to carry out a controlled and randomized clinical trial to evaluate the effectiveness of endodontic treatment non-instrumental (NIET) in deciduous teeth with CTZ paste (antibiotic-based paste) compared with the effectiveness of Guedes-Pinto Paste (iodoform-based paste).

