### **2.2 Experimental Design**

The present work is characterized as a controlled and randomized clinical trial of non-inferiority, with two parallel arms and allocation rate of 1:1 and which will be carried out at the Dental Clinic of the Metropolitan University of Santos (UNIMES). Because it is a randomized clinical trial and seeking greater transparency and quality of this research, we will use the CONSORT recommendations (Consolidated Standards of Reporting Trials). The study protocol was registered on the international platform of clinical trials ClinicalTrials.gov, with registration number NCT04587089

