### 3. Expected Results

Through the present work, we will be able to assess whether there will be a difference in effectiveness between the proposed treatments, as well as whether Guedes-Pinto paste in the NIET technique will present equal or better clinical and radiographic results when compared to the CTZ paste.

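### The trial is declared and sized as non-inferiority with a 15% limit, but the named group comparison (Student's t or Mann-Whitney) does not suit a success/failure outcome and is not linked to that limit.

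*Protocol*

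**What the plan says.** Section 2.2 of the protocol describes a "controlled and randomized clinical trial of non-inferiority, with two parallel arms and allocation rate of 1:1". Section 2.4 assumes "a 12-month success rate for the CTZ paste of 86.4"% and continues: "The non-inferiority limit was considered as 15%, power of 80% and significance level of 5%, which resulted in 38 teeth per group". After additions for losses and for children with more than one tooth, the target is 60 teeth per group.

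Section 2.9 makes the clinical evaluation the primary outcome, with follow-up at 1, 3 and 6 months, and sorts each treated tooth into success or failure.

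Section 2.10 is the analysis plan. It has five elements:
- Kaplan-Meier to estimate tooth survival, with the tooth as unit.
- An intention-to-treat analysis of successes and failures.
- The group comparison: "For comparison between the two groups, Student's t test or Mann-Whitney test will be performed, depending on the normality of the data".
- Poisson regression for the influence of some variables.
- A 5% significance level throughout.

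The Summary repeats all of these except the intention-to-treat sentence. Neither place mentions non-inferiority, the 15% limit or a confidence interval.

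Section 3 says the trial will show whether the treatments differ and "whether Guedes-Pinto paste in the NIET technique will present equal or better clinical and radiographic results when compared to the CTZ paste". Section 2.1 words the aim as treatment "with CTZ paste (antibiotic-based paste) compared with the effectiveness of Guedes-Pinto Paste (iodoform-based paste").

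**The concern.** A non-inferiority claim requires evidence that the test paste is not worse than the reference by 15 points or more. The comparison in section 2.10 asks a different question: whether the two pastes differ at all. Failing to reject no difference does not show that the difference is smaller than 15 points, and the smaller the trial, the easier that failure becomes.

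The rule for choosing the test is also unsuitable. A success/failure variable takes two values and cannot be normal, so a normality check cannot sensibly choose between the tests. Neither test handles censored times, although section 2.10 opens with Kaplan-Meier for the primary outcome.

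At stake is whether the declared objective has any stated analysis that answers it.

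**Working it through.** **Does anything in section 2.10 use the limit?**
- Kaplan-Meier is there to estimate survival. It supplies no group comparison by itself.
- The intention-to-treat sentence says that successes and failures are considered. It gives no test and no limit.
- Student's t and Mann-Whitney are the only methods named for comparing the groups. No null value other than zero is given.
- Poisson regression is for the influence of variables. It could include treatment, but nothing ties it to 15%.

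So the limit appears in section 2.4 only.

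**The plan's own figure.** With equal true rates, n per group = 2p(1-p)(z(1-α) + z(0.80))² / 0.15², with p = 0.864. This gives 64.6, so 65, at one-sided 5%, and 81.98, so 82, at one-sided 2.5%. The stated 38 is not reproduced. It appears if Guedes-Pinto success is set at 90% (one-sided 5%), which the protocol does not say. The inflation does fit: 38 × 1.6 = 60.8, against 60. The sizing is a separate matter and the present point does not depend on it.

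**Inputs for the size of the problem.**
- CTZ success 86.4% (section 2.4; a 12-month rate).
- Limit taken as 15 percentage points (the scale is not stated).
- Guedes-Pinto success at the limit: 86.4 - 15 = 71.4% (assumption).
- Teeth per group: 38 and 60 (section 2.4), and 48 = 60 × 0.8, that is, 60 less 20% losses.
- Teeth treated as independent (assumption).

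**Chance that the named test is non-significant when Guedes-Pinto is worse by the full limit.** All pairs of success counts were enumerated with binomial probabilities. The tests were applied two-sided at 5%; Mann-Whitney was tie-corrected. The margin rule passes if d - z × SE > -0.15, where d is Guedes-Pinto minus CTZ and SE = √[(p₁(1-p₁) + p₂(1-p₂))/n] from the observed proportions.

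| Teeth per group | t non-significant | Mann-Whitney non-significant | Margin rule wrongly passes, one-sided 5% | Same, one-sided 2.5% |
|---|---|---|---|---|
| 38 | 64% | 64% | 5.6% | 2.7% |
| 48 | 56% | 57% | 5.6% | 3.0% |
| 60 | 47% | 48% | 5.5% | 2.7% |

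A hand check at 60 per group: SE = √[(0.864 × 0.136 + 0.714 × 0.286)/60] = 0.0732. Then 0.15/0.0732 = 2.05, and Φ(1.96 - 2.05) = 46%, close to the enumerated 47-48%.

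**Two examples.**
- 48 per group, CTZ 42/48 v Guedes-Pinto 36/48: d = -12.5 points, SE = 7.86 points, p = 0.12. The 90% interval is -25.4 to +0.4 and the 95% interval -27.9 to +2.9.
- 60 per group, 52/60 v 46/60: d = -10.0 points, SE = 7.01 points, p = 0.16. The 90% interval is -21.5 to +1.5 and the 95% interval -23.7 to +3.7.

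In both, the named test finds no significant difference, while either interval reaches well below -15 points. Non-inferiority is not shown.

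**Effect of several teeth per child.** If the 40% addition in section 2.4 is read as a design effect of 1.4 (assumption), an interval that ignores clustering has a true critical value of 1.645/√1.4 = 1.39 at nominal one-sided 5%. The false-claim rate is then about 8%. A margin-based interval therefore also needs to allow for clustering.

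**The case against.** Four objections deserve an answer.

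1. *Only the protocol is at hand, and a decision rule is often left to the SAP.* That limits the claim to this document: one cannot say that the limit will never be tested. It does not remove the point, because the protocol does not defer the comparison. It names one that does not fit the declared design.

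2. *Student's t on 0/1 data gives a usable interval for a difference in proportions.* This is correct. The lower limit of a 90% t-interval, set against -15 points, wrongly passes in 4.7%, 5.0% and 4.9% of trials at 38, 48 and 60 per group. So it would be too strong to say that no named method could ever serve. But section 2.10 does not use the t test in that way, and the argument does not help the Mann-Whitney branch.

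3. *Nothing says that a non-significant result will be read as equality.* A reader might infer it from the aim in section 3, but the protocol states no such rule. The 47-64% figures are wrong-conclusion rates only under that inference. Otherwise they are one minus the power of a difference test. This stands.

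4. *Sections 2.1 and 3 do not conflict.* A reader might see opposite directions in them. Section 2.1 is ordinary prose about two pastes and not a hypothesis; section 2.4 only assumes a CTZ rate; section 3 alone words a direction. This also stands: it is an ambiguity to clear up, not a contradiction.

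**Conclusion.** The point holds, within limits. A trial declared and sized as non-inferiority names as its group comparison two tests of no difference, chosen by a check that the outcome cannot meet, and no other analysis in section 2.10 is linked to the 15% limit. That mismatch follows from the text and rests on no numerical assumption. It should be corrected before analysis.

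The size is conditional. If non-significance were taken as equality, the chance of passing a paste that is 15 points worse would be roughly 47% to 64%, depending on the teeth analysed, against about 5-6% with a margin-based limit at one-sided 5%. This assumes true rates of 86.4% and 71.4%, a limit in percentage points, and independent teeth. It also carries a 12-month rate into a trial followed for 6 months.

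**What to change.** In section 2.10 and the Summary, replace the t/Mann-Whitney sentence for the primary outcome with the following elements:
- Estimate the difference in 6-month success, Guedes-Pinto minus CTZ, on the primary clinical outcome of section 2.9.
- Give its confidence interval with standard errors that allow for several teeth per child, for example by GEE or a cluster-robust variance.
- Claim non-inferiority only if the lower limit is above -15 percentage points.
- State whether the 5% level is one-sided (90% interval) or two-sided (95% interval), and use the same choice in section 2.4, which leaves it open.

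State in section 2.1 that CTZ is the reference, as sections 2.4 and 3 imply. Keep Student's t and Mann-Whitney for continuous variables only.

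The cost is wording in the Summary and sections 2.1, 2.4 and 2.10. No new data are needed. The sponsor should expect the margin test to be demanding: with equal true rates of 86.4% and 60 independent teeth per group, its power is about 77-79% at one-sided 5% and 67-68% at one-sided 2.5%, before losses and clustering.
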